## Abstract

**Background:**

In addition to pain, sickle cell anaemia (HbSS) complications include neurocognitive difficulties in attention and processing speed associated with low daytime and night-time oxygen saturation compounded by obstructive sleep apnoea (OSA). In the general population OSA is treated with continuous positive airways pressure (CPAP). The aim of this single-blind, randomised, controlled phase II trial is to compare auto-adjusting CPAP (APAP) with standard care to standard care alone in individuals with HbSS to determine whether the intervention improves attention and processing speed, brain structure, pain and quality of life.

**Methods/Design:**

Eligibility criteria include: ability to provide informed consent; age > 8 years; diagnosis of HbSS; and mean overnight saturation of < 90% for < 30% of the night (i.e. not meeting current criteria for overnight oxygen therapy). Key exclusion criteria are: overnight respiratory support; respiratory or decompensated cardiac failure; chronic transfusion; or contraindications to APAP therapy or magnetic resonance imaging (MRI).

Sixty individuals with HbSS (30 children and 30 adults) will be randomised to standard care + APAP or standard care alone for six months. Minimisation factors are: age group (8–11, 12–15, 16–22 and > 23 years); silent infarction on MRI; minimum overnight oxygen saturation > 90% or < 90%; and hydroxyurea use.

For APAP individuals, the intervention is administered at home. Adherence and effectiveness are recorded using software documenting hours of use each night and overnight oximetry. Participant support in terms of appropriate facemask and facilitating adherence are provided by an unblinded sleep physiologist.

The primary outcome is change in the cancellation subtest from the Wechsler scales. Secondary outcomes include general cognitive functioning, quantitative brain MRI, blood and urine chemistry, quality of life and daily pain via a smartphone App (GoMedSolutions, Inc) and, where possible MRI heart, echocardiography, and 6-min walk. These outcomes will be assessed at baseline and after six months of treatment by assessors blind to treatment assignment.

**Discussion:**

Altering oxygen saturation in HbSS may lead to bone marrow suppression. This risk will be reduced by monitoring full blood counts at baseline, two weeks, three months and six months, providing treatment as appropriate and reporting as safety events.

**Trial registration:**

ISRCTN46012373. Registered on 10 July 2015.

Protocol Version: 6.0 Date: 24th December 2015

Sponsor: University Hospital Southampton. Sponsor’s protocol code: RHMCHIOT53

## Background

Sickle cell anaemia (SCA; HbSS) is an inherited red blood cell disorder associated with painful crises, acute chest crisis, cardiac dysfunction and a high risk of clinical stroke and ‘silent’ infarction. Even in the absence of stroke, children and adults may develop cognitive deficits [1] that have a significant impact on quality of life. Processing speed appears be a particular problem in those with clinical and ‘silent’ cerebral infarction (SCI) [2, 3], but adults and children with SCA without SCI still show reduced speed of processing on the Wechsler scales [4–6], affecting other aspects of cognition [7]. Specific deficits in attention, working memory and other aspects of executive function are frequently reported [4, 8–11].

Low daytime and night-time oxygen saturation (SpO_2_), potentially exacerbated by sleep-disordered breathing, including snoring and obstructive sleep apnoea (OSA), are more common in SCA than in the general population [12]. As there is a paucity of population-based normative data for sleep physiology in children and adults, it is difficult to apply cut-offs for intervention in SCA, particularly as the threshold might be lower as acute hypoxic exposure causes sickle haemoglobin to polymerise [13]. When polysomnography is available, > 40% of unselected children with SCA have an obstructive apnoea hypopnoea index (OAHI) > 1, [12] and the majority have OAHI above the normal range [14]. As this is an expensive investigation, there are few data in unselected populations of adults with or without SCA, but in a recent study, all SCA adults with sleepiness or symptoms of sleep-disordered breathing, e.g. snoring, had an apnoea hypopnoea index of > 1 [15]. Compared with data from the general paediatric population, [16, 17] mean and/or minimum oxygen saturation on overnight pulse oximetry are lower in the majority of patients with SCA [12, 15, 18] (Howard et al., submitted).

In addition to the evidence for an association of oxygen desaturation with endothelial dysfunction, [19, 20] cerebrovascular disease [21] and stroke [22, 23], cardiac dysfunction [24] and hospital days for pain, [25] there is evidence for links with cognitive difficulties, [26, 27] in line with previous experimental and clinical evidence. Animal data show that intermittent hypoxia during sleep is associated with impaired spatial learning and hippocampal vulnerability [28]. In addition to the evidence for a link with cerebrovascular disease, [29] minimum oxygen saturation is associated with cognitive difficulties in OSA [30] in the adult general population and in other conditions, such as multiple sclerosis [31]. Magnetic resonance imaging (MRI) abnormalities have also been reported in relation to oxygen desaturation in SCA [32]. In 25 individuals with SCA but no evidence of SCI, a whole-brain voxel-wise MRI analysis of white matter (tract-based spatial statistics [TBSS]), showed a significant correlation of reduced daytime SpO_2_ and high radial diffusivity (RD) in the anterior corpus callosum (*p* < 0.05) [32]. The anterior corpus callosum contains fibres connecting the left- and right-hemisphere prefrontal cortex, underpinning important executive functions. These results suggest that chronic oxygen desaturation could play a vital role in the viability of frontal lobe white matter and so diffusion tensor imaging metrics may serve as biomarkers for monitoring therapeutic effects. Hippocampal volumetric deficits have been shown in children and adolescents with SCA [33]. In adults with OSA, cognition is compromised and hippocampal alterations seen on MRI have been reported; importantly, the effects of hypoxic exposure on cognition and hippocampal volume have been reported to be reversible [34].

In patients with SCA, reduced exercise tolerance is reported in daily living and observable during a 6-min walk test (6MWT). In addition, structural abnormalities on echocardiography [35] and cardiac MRI [36] are well recognised. There are, however, few published data on how cardiac function is related to sleep-disordered breathing [24] or changes during exercise [37] or whether these findings can be reversed.

There is therefore a case for exploring whether interventions to improve sleep-disordered breathing, OSA and nocturnal desaturation improve clinically relevant endpoints in SCA. Adenotonsillectomy is an invasive procedure which may not cure OSA [38]. Continuous positive airways pressure (CPAP) is standard treatment for OSA in adults but the potential discomfort of breathing against a continuous pressure of 10 cm water is not easy to justify unless there is polysomnographic evidence of frequent airway obstruction. For auto-adjusting continuous positive airways pressure (APAP), the continuous pressure is set to a more comfortable pressure of around 4 cm water and the pressure only rises to a preset maximum of, for example, 10 cm water when obstruction is detected by the machine, making it more appropriate for patients with only a few episodes of obstruction per night; [39] additional modalities may be effective for causes of sleep-disordered breathing other than OSA [40]. APAP is likely to improve minimum oxygen saturation by preventing desaturation in even minor degrees of airway obstruction. Although occasional adverse events (AEs) related to APAP are reported, we saw none in our previous pilot studies; the main problem with positive airways pressure interventions is non-compliance if the patient does not feel that the nuisance is worth any potential benefit.

In a small randomised trial of standard care vs APAP in children with SCA, all 12 were compliant for six weeks and both daytime and mean overnight oxygen saturation increased, the latter significantly [18]. A psychologist blind to treatment arm undertook five subtests of the Wechsler scales chosen to examine processing speed, attention and working memory. The primary endpoint, processing speed index, improved in the standard care as well as the treatment arm, possibly in part due to a practice effect. However, cancellation, a Wechsler subtest of visual attention as well as processing speed, showed statistically significant improvement only in the treatment arm [18]. In addition, in a pilot study (Prevention of morbidity in sickle cell disease, POMS 2a) (Howard et al., submitted) for this phase II study (POMS 2b), we compared safety and tolerability in children and adults for two alternative interventions: APAP and Nocturnal Oxygen Therapy (NOT). In a crossover design, after a week’s baseline, each intervention was used for one week, with a week-long washout between phases. Compared to baseline, individuals experienced small increases in daytime oxygen saturation and decreases in haemoglobin and for the week on both APAP and NOT, but there was no difference between interventions (Howard et al., submitted). Ten of 16 (62.5% [95% confidence interval = 38.6–81.5]) who completed qualitative interviews reported a preference for APAP (Howard et al., submitted). Practical advantages of APAP include the cost, size and portability of the APAP machine, an optional humidifier attachment to treat dry throat, an adjustable mask, optional addition of oxygen if required and capacity for remote compliance monitoring.

In the current POMS 2b Phase II study, ethical and practical considerations preclude blinding individuals and investigators, but the risk of bias in outcome assessment can be minimised by utilising cognitive and imaging endpoints assessed by blinded personnel. A single-blind design is justified as preliminary evidence suggests that treating OSA and improving oxygen saturation, for example, using overnight oxygen [41] or CPAP, [18, 42] might improve cognition and brain structure. APAP has a favourable risk–benefit profile; the main safety concern in altering oxygen saturation in SCA is the possibility of bone marrow suppression resulting in reductions in haemoglobin, red cell count, reticulocytes and erythropoietin [43].

### Aim

The objective of this single-blind, randomised, controlled phase II trial is to compare APAP with standard care in individuals with HbSS to determine whether six months of using the intervention improves attention and processing speed, brain and heart structure, pain and quality of life

## Methods and design

This is a single-blind randomised controlled phase II trial consisting of two separate cohorts of people with HbSS (children and adults) recruited through two London National Health Service hospitals in the UK (Guy’s and St Thomas’ NHS Trust and King’s College Hospital NHS Trust, both academic centres as part of King’s Health Partners). Though some pooled analyses may be conducted, the cohorts are independent and will be analysed separately. Informed consent/assent will be obtained from all participants in the study. After randomisation, individuals assigned to APAP will be provided with a REMstar® Auto System, which is an APAP device designed for the treatment of OSA and is supplied by Respironics. When set in the Auto‐APAP mode, the system will monitor breathing during sleep and automatically adjust the pressure to meet therapeutic needs. Individuals in the APAP arm will use this intervention nightly for six months. Individuals randomised to standard care will have treatment according to routine National Health Service procedure for sickle cell disease for six months post randomisation.

The intervention involves wearing a mask for several hours most nights, so it is difficult to justify a sham treatment arm of six months of overnight respiratory support. The outcomes will be assessed by study personnel blind to treatment arm so that although the family and some professionals involved in data collection know the treatment allocation, the assessors of endpoints, including cognitive function, imaging, pain frequency and quality of life, will not know the treatment assignment. All study personnel not directly involved in treatment administration and compliance will be blinded to randomisation assignment until the blind is broken for each cohort. Blinded study personnel include data managers and the trial statistician, as well as assessors of endpoints.

APAP dose reductions are permitted if required, e.g. in the case of AEs. Discontinuation of participants from the trial will occur if there is withdrawal of a child’s assent to participate or participant/parental/guardian withdrawal of consent to participate or loss to follow-up; wherever possible the primary and secondary endpoint will be collected.

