### Randomisation

Central randomisation by computer by the company ‘Sealed Envelope’ will be used with a minimisation algorithm [44] incorporating a random element, stratifying by baseline oximetry minimum overnight saturation (<90% vs ≥ 90%), whether or not a participant is currently prescribed hydroxyurea, presence or absence of infarction on MRI and age group: 8–11 vs 12–15 years in children, and 16–22 vs ≥ 23 years in adults. To ensure maximum balance is achieved across the stratification factors, minimisation will be carried out on these factors separately. Individuals will be randomised to APAP + standard care or standard care alone. The coordinator will be informed of the allocation by email and will arrange for the respiratory physiologist to set up APAP at home for those randomised to APAP.

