**Fig. 1 Fig1:**
[figure not shown]
Data collection

Study flow from randomisation through follow-up is shown in Fig. 2. Two weeks after commencement of randomised treatment, individuals will have a face-to-face review for AEs and adherence, and will have daytime oximetry and blood and urine tests. Participants will also have a repeat overnight oximetry at home. Face-to-face assessments for AEs, adherence, daytime oximetry, blood and urine will also take place at months 3 and 6. At months 1, 2, 4 and 5, individuals will be contacted by the study coordinator for review of AEs, treatment adherence and administration of the sickle cell pain burden questionnaire [48].

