### Pain

Monitoring of daily pain will occur daily for two weeks at two separate time-points: baseline and end of study. Assessments will be performed using a Smartphone e-Diary (GoMed Solutions Inc), taking < 5 min per day to complete, which downloads anonymous data to a web-based database. This application collects information including whether or not pain was experienced and if it was, further questions on pain characteristics as follows: (1) current pain, using a 0–10 electronic numerical rating scale (e-NRS); (2) the highest e-NRS in past 24 h; (3) the lowest e-NRS in past 24 h; (4) the average-e-NRS in the past 24 h; (5) location of pain on a body outline diagram; (6) how much pain interfered with everyday activities in past 24 h; and (7) descriptors of pain to characterise its nature as neuropathic or nociceptive. The same information may also be collected on a paper form. In addition, pain characteristics and descriptors will be collected at the end of every month via a phone call using the Pain burden questionnaire [48]. Pain-related healthcare visits over the entire period, including admissions for pain (reported as expected serious adverse events), will be compared between the two arms to assess whether the intervention has an impact on hospital attendance and admission.

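### Pain and quality of life are stated to be assessed blind, but unblinded participants or parents rate them, and a coordinator who knows the arm gives the pain burden questionnaire

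*Protocol article*

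**What the plan says.** The section Methods and design explains why a sham was judged hard to justify. It concedes that "the family and some professionals involved in data collection know the treatment allocation", and then states in the same sentence that "the assessors of endpoints, including cognitive function, imaging, pain frequency and quality of life, will not know the treatment assignment". The Abstract lists the secondary outcomes, among them quality of life and daily pain recorded by smartphone app, and adds: "These outcomes will be assessed at baseline and after six months of treatment by assessors blind to treatment assignment".

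Other sections describe who knows the allocation and who supplies the data:

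- Background: "ethical and practical considerations preclude blinding individuals and investigators". The stated remedy is that "the risk of bias in outcome assessment can be minimised by utilising cognitive and imaging endpoints assessed by blinded personnel". Pain and quality of life are not named there.
- Randomisation: "The coordinator will be informed of the allocation by email". The same role then arranges for APAP to be set up at home.
- Data collection: "individuals will be contacted by the study coordinator for review of AEs, treatment adherence and administration of the sickle cell pain burden questionnaire". This contact is planned for months 1, 2, 4 and 5.
- Pain: daily pain is entered in a smartphone diary on a 0–10 scale, and "pain characteristics and descriptors will be collected at the end of every month via a phone call using the Pain burden questionnaire".
- Quality of life: the instruments are the PedsQL with its sickle module, the CHU-9D and the EQ-5D.
- Cognitive outcomes: the BRIEF is completed by a parent or by the participant. The other tests are given by a psychologist who is blind to arm.

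**The concern.** For an outcome that a person reports about their own state, the assessor is that person, or the parent who answers for a child. If that person knows the arm, the outcome is not assessed blind, whoever scores the form afterwards. Where an interviewer puts the questions and also knows the arm, a second route for bias opens.

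Pain and quality of life are named in the Aim. The Discussion counts them, with cognitive function, as the three domains important to patients on which the trial will inform clinicians. A reader who takes the blinding statement at face value would treat an arm difference in pain or quality of life as protected in the same way as a difference in the psychologist-administered tests. Expectation in an unsham-controlled device trial, or the manner of an interviewer who knows the arm, could produce such a difference without any treatment effect.

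**Working it through.** No arithmetic applies. The point depends on no sample size, standard deviation, effect size or error rate, and the plan states no figure to reproduce. The check is to ask, for each outcome, who rates it, who collects it, and whether that person knows the allocation.

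1. **Daily pain (e-diary).** The rater is the participant, who enters numerical ratings and descriptors (Pain). Participants are not blinded (Background; Methods and design). Not blind, contrary to the Abstract.
2. **Pain burden questionnaire, months 1, 2, 4 and 5.** The respondent is unblinded, as in step 1. The questionnaire is given by the study coordinator (Data collection), and the coordinator receives the allocation by email (Randomisation). I take these to be one role. If they were two people, the result would be the same, because the caller reviews treatment adherence in that contact and would learn who has a device. Neither respondent nor interviewer is blind.
3. **Quality of life (PedsQL, CHU-9D, EQ-5D).** The section does not say in words who completes these or who hands them out. That the participant or parent is the rater is inferred from the type of instrument. On that inference, not blind, contrary to both statements.
4. **BRIEF.** Explicitly parent- or self-report (Cognitive outcomes). Not blind, although it falls under the cognitive function named in the claim.
5. **Cancellation and the other psychologist-administered tests.** The psychologist is blind to arm (Cognitive outcomes). The claim holds.
6. **Brain MRI.** The neuroradiologist's reading and the quantitative analysis are both blind to arm (Brain MRI). The claim holds.

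The claim therefore holds for steps 5 and 6 and fails for steps 1 to 4. The Background already confines the argument to cognitive and imaging endpoints, so the wider list in Methods and design and in the Abstract is also inconsistent with the protocol's own rationale. The Background's phrase would still take in the BRIEF unless it is narrowed to psychologist-administered tests.

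**The case against.** The strongest reply is that the protocol hides nothing. It says openly that individuals, families and some data collectors know the arm, and it blinds only personnel outside treatment administration and compliance. On this reading it separates collecting data from assessing endpoints, and the coordinator belongs to the disclosed unblinded group. That explains the coordinator's position, but it does not rescue the claim. The sentence that makes the concession goes on to say that assessors of pain frequency and quality of life will not know the arm. Blind data managers and a blind statistician protect the handling of the data, not the answer given.

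A second reply is that pain frequency might mean pain-related visits and admissions, which could be counted blind from records. That is possible for those counts, but the Abstract makes the claim for daily pain from the app.

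A third reply is about weight, and it stands. Only secondary outcomes are involved, and Statistical analysis already urges caution beyond the primary outcome.

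A reader might infer more than the documents support:

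- *That only performance tests and imaging are free of the problem.* The outcomes also include daytime oximetry, laboratory measures and cardiac investigations. Neither participant rating nor coordinator interview is shown to affect them.
- *That the trial will report pain and quality of life as blind-assessed.* Nothing in the article says how those results will be labelled.
- *That the false-positive rate can be quantified.* Any size of reporting shift would be an outside assumption. The correlation of 0.5 in Sample size belongs to cancellation, and pain with repeated collection points is to be analysed by mixed models.

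**Conclusion.** The stated blinding does not hold for participant- or parent-reported pain, quality of life and BRIEF. For the pain burden questionnaire at months 1, 2, 4 and 5 the interviewer is unblinded as well. This should be corrected, because the article claims a design property that these outcomes do not have. It does not threaten the primary outcome, its test, the sample size or the brain MRI reads.

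The size of any bias cannot be derived from the documents, and no figure is offered. The conclusion rests on two readings: that the quality-of-life instruments are completed by the participant or a parent, and that the coordinator who receives the allocation is the one who makes the calls. The second is not essential, since the adherence review would reveal the arm anyway.

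**What to change.** 1. In Methods and design and in the Abstract, limit the blind-assessor statement to outcomes for which a blind assessor is in place: the psychologist-administered cognitive tests and the imaging reads, in line with the Background. If other measures, such as the cardiac investigations, are in fact read blind, name them.
2. State that pain, quality of life and the BRIEF are reported by unblinded participants or parents, and that the pain burden questionnaire at months 1, 2, 4 and 5 is collected by a coordinator who knows the allocation.
3. Say that between-arm differences on these outcomes are open to reporting bias and, for the questionnaire, to interviewer bias, and interpret them on that basis.

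The cost is wording, and a weaker claim for two of the three domains in the Discussion. No analysis or sample size changes.

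Separating the questionnaire from the adherence contact would remove the interviewer route, though not the participant's own knowledge of the arm. It suits participants not yet started, or a later trial. It is not required here: Trial status reports 30 + 28 = 58 of the planned 60 randomised by 30 March 2017, and a change of collection mode at that stage would mix modes within the trial.
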